## Abstract

**Background:**

Transdisciplinary approaches can streamline processes and build workforce capacity by blurring traditional responsibilities and integrating aspects of care. Emerging evidence shows transdisciplinary approaches can improve time-efficiency, quality of care and cost-effectiveness across various healthcare settings, however no empirical study is based on an acute stroke unit.

**Methods:**

The SPIRIT checklist was used to guide the content of the research protocol. The study is a pragmatic pre−/post- mixed methods four-phase study with a 3-month follow up, based at the Mater Hospital Brisbane. Participants experiencing stroke symptoms will be recruited as they are admitted to the acute stroke unit. Patients presenting with mild stroke symptoms or Transient Ischaemic Attack will be allocated to Phase 1 (baseline) or Phase 2 (implementation), while patients presenting with moderate to severe stroke symptoms will be allocated to Phase 3 (baseline) or Phase 4 (implementation). Participants in baseline Phases 1 and 3 will receive standard allied health assessment, while participants in implementation Phases 2 and 4 will receive the novel transdisciplinary assessment. For the primary aim, allied health professionals will time their assessments to evaluate time taken to administer a novel transdisciplinary assessment, compared to usual discipline-specific assessments. Non-inferiority of the novel transdisciplinary assessment will also be explored in terms of patient safety, compliance to national standards, use of the assessment, and stakeholder perceptions. A retrospective medical record audit, staff focus group, patient/staff surveys, and patient phone interviews at 3-months will be completed. Quantitative results will be estimated using general linear and logistic regression models in Stata 15.1. Qualitative results will be analysed using frequency counts and NVivo software. An economic evaluation will be performed using three scopes including the allied health assessment, hospital admission, and patient outcomes at 3-months.

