### Study aim

The primary aim of this research is to understand the benefits (or otherwise) of implementing a novel Transdisciplinary Initial Neurological Screening Assessment (TINSA) on the MHB ASU. We hypothesise that compared to the existing discipline-specific allied health stroke assessments, utilising the TINSA will reduce allied health assessment time by at least 20 minutes during the initial occasion of service, without reducing quality of care. Secondary aims are to evaluate use of AHP time across the participant hospital admission, quality of care provided by AHPs in terms of patient safety and compliance to national stroke guidelines, clinical utility of the novel TINSA, economic implications of implementing the novel TINSA, patient and staff satisfaction, staff interprofessional trust, and staff confidence to complete and share transdisciplinary tasks.

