### Outcome measures

A complete list of outcome measures is provided in Table 1.

**Table 1 Tab1:** List of outcome measures

Outcome	Measures
Time-efficiency	• Total time of allied health stroke assessments • Time from admission to enactment of social work referral • Time from admission to commencement of allied health intervention/rehabilitation • Occasions of face-to-face service with AHPs (occupational therapy, physiotherapy, speech pathology, social work) • Number of referrals to AHPs (occupational therapy, physiotherapy, speech pathology, social work) where no intervention or further assessment is indicated • Number of patients who received allied health assessment but had a negative stroke diagnosis on MRI • Time from admission to discharge from allied health (occupational therapy, physiotherapy, speech pathology) • Length of hospital stay
Cost savings	• Economic evaluation to determine difference in utilisation of hospital resources, such as bed space and AHP time
Quality of care (patient safety)	• Total number of adverse events during the hospital admission that may be related to allied health input (falls, extension of stroke, aspiration pneumonia, pressure injuries) • Missed allied health referrals (other than those due to a change in condition) • Failed discharge, defined as unplanned readmission within 30 days not related to a new episode of care
Quality of care (compliance to national stroke guidelines)	• Time from admission to allied health assessment (occupational therapy, physiotherapy, speech pathology) • Time from admission to commencement of allied health intervention (occupational therapy, physiotherapy, speech pathology) • Time from admission to mobility assessment • Time from admission to communication assessment
Utility of the novel TINSA	• Number of sections attempted/completed on the novel TINSA • Number of “stop and refer” prompts used on the novel TINSA • Number of allied health referrals identified from the novel TINSA
Patient and staff satisfaction	• Patient satisfaction survey • Staff satisfaction survey • Staff focus group
Staff trust and confidence	• Staff interprofessional trust surveys • Staff confidence surveys (pre/post competency training) • Staff building confidence surveys (monthly intervals)

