### Statistical analysis

#### Statistical power

The power calculation demonstrates the required participant number per phase to sufficiently power the study to find a minimal clinically important difference in the primary aim. The following time estimates represent the expert opinions of the AHPs working on the MHB ASU. The variation in time taken to complete discipline-specific occupational therapy, physiotherapy and speech pathology initial stroke assessment may range from 80 to 210 minutes total. The smallest clinically important improvement in time taken to allied health stroke assessment would be a decrease of 20 minutes in average total assessment time (i.e., enough time to complete another occasion of service or clinical task). Assuming a similar distribution of patients in each assessment group, a significance level of 0.05, 80% power and a standard deviation of 25 minutes, 26 patients per group will be required to detect a 20-minute difference in total assessment time.

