#### Quantitative data analysis

For each participant group, two periods of time to measure standard discipline-specific allied health assessment and the TINSA assessment will be evaluated and compared. Patient characteristics, outcomes and quantitative survey responses will be summarised for each assessment group using frequency and percent for categorical variables, means and standard deviations for approximately normally distributed continuous variables, and medians and interquartile ranges for non-normally distributed continuous variables. Differences between assessment groups will be estimated using the general linear model for continuous outcomes and logistic regression for categorical outcomes. Balance of potential confounders between the assessment groups will be investigated and multivariable adjustment will be employed where there is an apparent confounding effect. Results will be presented as differences (continuous outcomes) and odds ratios (categorical outcomes) with 95% confidence intervals. All analyses will be performed using Stata 15.1 (Stata Corp, College Station, TX) and a *p*-value < 0.05 will be considered statistically significant throughout all inferential analysis.

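### Non-inferiority on quality of care is named as an objective, but the article fixes only p < 0.05 difference tests and a sample size set for assessment time, so a non-significant result could not support it

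*Protocol article*

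**What the plan says.** The Methods part of the abstract states: "Non-inferiority of the novel transdisciplinary assessment will also be explored in terms of patient safety, compliance to national standards". The same sentence adds use of the assessment and stakeholder perceptions. Under Study aim, the hypothesis is that the TINSA "will reduce allied health assessment time by at least 20 minutes during the initial occasion of service, without reducing quality of care"; the next sentence lists quality of care among the secondary aims.

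Under Quantitative data analysis, the method is: "Differences between assessment groups will be estimated using the general linear model for continuous outcomes and logistic regression for categorical outcomes". On reporting: "Results will be presented as differences (continuous outcomes) and odds ratios (categorical outcomes) with 95% confidence intervals". The decision criterion is that a p-value below "0.05 will be considered statistically significant throughout all inferential analysis". No margin appears in the article.

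Under Statistical power, 26 patients per group are derived for a 20-minute difference in total assessment time, with "a significance level of 0.05, 80% power and a standard deviation of 25 minutes". No quality outcome enters that calculation. Table 1 lists the utility measures, the first being: "Number of sections attempted/completed on the novel TINSA". The other two are the stop-and-refer prompts used on the TINSA and the referrals identified from it.

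**The concern.** A test against no difference asks whether an effect can be detected. Non-inferiority asks whether a loss larger than a stated amount can be ruled out. A p-value above 0.05 answers neither question when the sample is small, because it is compatible with no harm and with substantial harm. The article names the second question and fixes a criterion only for the first.

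This matters because the time saving is of value only if quality is preserved; the Discussion itself describes a dual focus on efficiency and quality. If the quality side cannot be judged by the stated criterion, the second half of the hypothesis cannot be confirmed, whatever the data show.

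There is also a gap in logic. Something can be non-inferior only to a comparator, and the measures of TINSA use do not exist in Phases 1 and 3.

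**Working it through.** **1. The plan's own figure.** Inputs from Statistical power: difference 20 minutes, SD 25, alpha 0.05, power 80%. The normal approximation gives n = 2 × (1.960 + 0.842)² × 25² / 20² = 24.5, so 25 per group. The two-sided t-test version gives 25.5, so 26. The stated 26 is reproduced and is correct for assessment time.

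**2. Power to detect a doubling of harm.** The article gives no event rates, so the baseline rates below are assumptions. Power is the exact binomial sum, over all pairs of event counts, of the probability of pairs giving two-sided p < 0.05. The 52 v 52 columns assume simple pooling of the two phase pairs with the same rate in each.

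| Assumed baseline → doubled | Fisher, 26 v 26 | Chi-square, 26 v 26 | Fisher, 52 v 52 | Chi-square, 52 v 52 |
|---|---|---|---|---|
| 5% → 10% | 1.5% | 8% | 7% | 15% |
| 10% → 20% | 9% | 18% | 21% | 29% |
| 20% → 40% | 25% | 37% | 52% | 62% |
| 30% → 60% | 48% | 58% | 85% | 90% |

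**3. What an interval could exclude.** Take 2/26 events (7.7%) in each phase. The Wilson limits for one phase are 2.1% and 24.1%. The Newcombe half-width is √[(0.241 − 0.077)² + (0.077 − 0.021)²] = 0.174, so the 95% interval for the difference is −17 to +17 points. With 0/26 events, the exact (Clopper-Pearson) upper limit for the rate is 1 − 0.025^(1/26) = 13.2%.

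**4. Non-inferiority with a margin.** Suppose, as an illustration only, a margin of 10 points and a true rate of 5% in both phases. The chance that the Newcombe upper limit falls below 10 points is 25% at 26 v 26 and 51% at 52 v 52. By the normal approximation, the smallest margin that can be shown with 80% power at 26 v 26 is (1.960 + 0.842) × √[2p(1 − p)/26]. That is 17 points at p = 5%, 23 at 10% and 31 at 20%.

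**5. Estimability of the odds ratio.** The probability that at least one phase of a pair has no events is 1 − [1 − (1 − p)²⁶]². At 5%, (0.95)²⁶ = 0.264, which gives 1 − 0.736² = 46%. At 10%, (0.90)²⁶ = 0.065, which gives 12.5%. At 20% it is below 1%. With a zero cell, an ordinary logistic odds ratio has no finite estimate on the log scale.

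**6. Comparator for use of the assessment.** All three utility measures in Table 1 are recorded on the TINSA form. The baseline phases use discipline-specific assessments, so there is no value to set beside them.

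**The case against.** The strongest reply is that the article does not go as far as a reader might fear. A reader might infer that a non-significant result will be declared safe. The article does not say so: the abstract speaks of exploring, the analysis section promises 95% intervals, and Data management and monitoring has a separate fortnightly review that reacts to an increase in adverse outcomes without requiring significance. That stands, and the inference is not made here. The review rule, however, has no threshold and is not an analysis of non-inferiority.

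A reader might also infer that a doubling of harm would almost never be seen. That too is not supported in general. It is fair at rates of about 5% or below, but at 20% to 30% Fisher power is 25% to 48% per pair and higher when pooled. The main safety outcome combines falls, stroke extension, aspiration pneumonia and pressure injuries, so a low rate cannot be presumed. Fisher's test is also more conservative than the planned logistic model, which is why chi-square results are shown.

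Non-inferiority appears only in the abstract, quality of care is also listed as a secondary aim, and a margin could sit in a plan not shown. These points reduce the weight but do not remove the mismatch: the article itself sets p < 0.05 for all inferential analysis, and a margin-based rule would have to change that. Finally, the compliance measures are times from admission, analysed as continuous outcomes. The event-rate figures do not apply to them, though the absence of a bound does.

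**Conclusion.** The mismatch holds on the text. Non-inferiority is named and preserved quality is written into the hypothesis, but the only fixed criterion is a difference test at p < 0.05, with intervals and no bound, in a study sized for time alone. A non-significant result could not support the claim. For use of the assessment, no comparison is possible.

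The size depends on assumed event rates. For uncommon harms (5% to 10%), power to detect a doubling is 1.5% to 9% by Fisher's test and 8% to 18% by chi-square in one phase pair; pooling raises this to at most 29%. For commoner outcomes (20% to 30%) it is moderate: 25% to 58% per pair. These figures also assume that 26 patients are reached in each phase. That number is a requirement for the time outcome, and Phases 3 and 4 are limited to three months each, so it is not assured there. The 26 itself is not in question. This should be corrected, but it does not undermine the primary time comparison.

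**What to change.** Choose one of two routes:

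- Drop the term non-inferiority, and treat quality of care as estimation instead of a tested part of the hypothesis.
- State a margin on the risk-difference scale for one or two key quality outcomes, judge the 95% interval against it, and acknowledge the limited power.

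In either case:

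- Report risk differences with Newcombe or exact 95% intervals for adverse events, missed referrals and failed discharges, by phase pair and pooled with stratification by severity.
- State the largest increase in harm that the data do not exclude.
- State that p > 0.05 will not be taken as preserved quality.
- Remove use of the assessment from the non-inferiority list and report it descriptively.

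The cost is wording and a different effect measure on data already being collected. The downside is a more modest safety claim.

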**Discussion:**

When designing the study, pragmatic factors related to staff willingness to be involved, patient safety, and existing clinical pathways/processes were considered. To address those factors, a co-design approach was taken, resulting in staff buy-in, clinically relevant outcome measures, and the pre−/post- four-phase study design.

**Trial registration:**

Australian New Zealand Clinical Trials Registry (ANZCTR), ACTRN12621000380897. Registered 06 April 2021 - retrospectively registered, https://www.anzctr.org.au/Trial/Registration/TrialReview.aspx?id=381339&isReview=true

**Supplementary Information:**

The online version contains supplementary material available at 10.1186/s12913-022-08926-y.

## Background

Allied health professionals (AHPs) are central to the provision of quality stroke services. The Australian stroke guidelines state that all people experiencing stroke should receive physiotherapist assessment within 24–48 hours of admission to hospital, and assessment by occupational therapists and speech pathologists within 48 hours of admission [1]. While each AHP has a clearly defined role, overlapping skills and knowledge result in some assessment tasks and questions being administered repeatedly by different clinicians [2–4]. At the Mater Hospital Brisbane (MHB) Acute Stroke Unit (ASU), the physiotherapist, occupational therapist, and speech pathologist assess patients presenting with stroke separately. However, these discipline-specific assessments overlap, for example the physiotherapist and occupational therapist both assess upper limb function and gather information on previous level of function and the home environment. Such duplication across allied health assessments is unnecessary, inefficient, and AHP time could be better utilised.

A transdisciplinary approach to allied health stroke assessment could streamline AHP services, which is pertinent given the increasing consumer demand for stroke care. In Australia, the number of new stroke diagnoses per year is predicted to grow from 27,000 in 2020 to exceed 50,000 by 2050 [5]. Transdisciplinary approaches are defined by their potential to build workforce capacity by blurring lines of traditional responsibilities and integrating aspects of care (such as assessment) to enable a single team member to deliver the occasion of service [6–9]. There is emerging evidence that demonstrates, when compared to usual care, hospital-based allied health transdisciplinary teams improve AHP time-efficiency, quality of care, and are cost-effective [3, 10, 11]. No negative or harmful outcomes were reported [3, 10, 11]. When pilot testing the allied health transdisciplinary assessment to be used in this study, the authors demonstrated a mean time saving of 103 minutes when the transdisciplinary assessment was used (42 minutes), compared to usual single-dicipline assessments (145 minutes) [12]. A time saving of 103 minutes could be clinically significant. For example, AHPs would have more time available to commence rehabilitation earlier in the patient episode of care, thereby aligning the service more closely with national stroke guidelines [1]. The pilot testing served as proof of concept for the study proposed in this paper. To the author’s knowledge, no other empirical studies have evaluated transdisciplinary approaches on ASUs. Due to the low volume of empirical evidence pertaining to transdisciplinary approaches on ASUs, alongside the potential for transdisciplinary approaches to streamline stroke services, empirical research is warranted in this field.

## Methods/design

The SPIRIT checklist was used to guide the content of the protocol (see Additional file 1).

### Study aim

The primary aim of this research is to understand the benefits (or otherwise) of implementing a novel Transdisciplinary Initial Neurological Screening Assessment (TINSA) on the MHB ASU. We hypothesise that compared to the existing discipline-specific allied health stroke assessments, utilising the TINSA will reduce allied health assessment time by at least 20 minutes during the initial occasion of service, without reducing quality of care. Secondary aims are to evaluate use of AHP time across the participant hospital admission, quality of care provided by AHPs in terms of patient safety and compliance to national stroke guidelines, clinical utility of the novel TINSA, economic implications of implementing the novel TINSA, patient and staff satisfaction, staff interprofessional trust, and staff confidence to complete and share transdisciplinary tasks.

### Study setting

This is a single-centre metropolitan clinical study, based at the MHB ASU. The ASU is a dedicated 7-bed unit within the Mater Centre for Neurosciences, which is a mixed publicly and privately funded hospital ward. The ASU is serviced by neurologists, nurses, occupational therapists, physiotherapists, speech pathologists, social workers, dieticians, and allied health assistants.

### Study design

The clinical study of the TINSA is a pragmatic pre−/post four-phase mixed methods study with non-randomised comparative groups, a convergent parallel design, and longitudinal follow-up at 3-months after hospital admission. The main quantitative element of the study incorporates descriptive and cross-sectional analytic components and measures designed to evaluate and compare four periods of time during which existing and new transdisciplinary stroke assessments are evaluated (see Fig. 1). Only the allied health stroke assessment component of the patient admission to the MHB ASU will be evaluated, and subsequent allied health input will continue as per usual care. Phase 1 (baseline, usual care) and Phase 2 (implementation of TINSA) will recruit participants experiencing symptoms of mild stroke or Transient Ischaemic Attack (TIA) and evaluate usual assessment compared to the novel TINSA (respectively). Between Phases 1 and 2, a 1-month transition phase will take place to allow staff to become familiar with the novel TINSA, complete competency training, and practice the new clinical process. Phase 3 (baseline, usual care) and Phase 4 (implementation of TINSA) will recruit participants experiencing moderate to severe stroke symptoms to evaluate usual assessment compared to the novel TINSA (respectively). Phases 3 and 4 will occur in parallel with Phase 2 and be time-limited (3 months/phase) due to time constraints on the ASU. Due to the nature of the clinical processes and staffing on the MHB ASU, neither randomisation nor blinding are feasible.

**Fig. 1 Fig1:**
[figure not shown]
Transdisciplinary study design

### Participants

Potential study participants will include eligible patients and staff working in the ASU.

#### Inclusion criteria

In Phases 1 and 2, patients who are admitted to the MHB ASU with a possible or confirmed diagnosis of mild stroke or TIA are eligible to participate in the study. Mild stroke or TIA are defined as presentations of mild or resolved neurological symptoms including limb strength above grade 3/5; without visuospatial or sensorimotor neglect; able to communicate verbally; able to follow a one-stage command. From the eligible participants, only those who score ≥ 19/30 on the Montreal Cognitive Assessment (MoCA) (participants with no significant cognitive deficits [13]) will be asked to complete the patient satisfaction survey and follow-up phone call at 3-months after admission.

In Phases 3 and 4, patients who are admitted to the MHB ASU with a possible or confirmed diagnosis of moderate to severe stroke are eligible to participate in the study. Moderate to severe neurological symptoms include limb strength below grade 3/5; visuospatial and/or sensorimotor neglect; aphasia; cognitive impairment. All eligible participants (and/or an authorised representative) will be asked to participate in a follow-up phone call 3-months after admission.

All consenting staff who work on the MHB ASU during the study period will be eligible for inclusion in the study.

